#### Qualitative outcomes analysis

The analysis will be conducted using Dedoose software (version 9.0.17) by a PhD student and a social psychologist. A comparative thematic analysis of the collected content will be conducted by using the proposal by Braun and Clark, which included the following steps: familiarisation with the data, coding the data using the CFIR domains and subdomains by the two researchers, searching for themes through iterative discussion between the two researchers, comparing the themes obtained with the CFIR domains and refining the coding and illustrating with verbatims.

#### Health economic analysis

An incremental cost-utility ratio and an incremental cost-effectiveness ratio (ICER) will be calculated by dividing the difference in mean costs between the intervention group and the control group by the difference in mean effectiveness, as the French National Authority for Health (HAS) recommended. ICERs will be estimated for the two health economic endpoints, expressed as (1) the cost per QALY gained and (2) the cost per patient continuing PA at 12 months between the experimental arm and the placebo arm. These ICERs will also be produced for each department to complete the context analysis. The time horizon corresponding to the study period is 12 months; no discounting will be performed, as recommended. QALYs will be calculated based on responses to the EQ-5D-5L questionnaire, transformed into utilities and mortality data obtained during the study, if any. The efficacy endpoint for the cost-effectiveness analysis will be the number of patients who continued PA at 12 months, as measured in the study. Costs will be expressed in euros. The ICER will be positioned on the cost-effectiveness plan. Using the non-parametric bootstrap method, statistical uncertainty will be considered to construct a 95% CI and a scatter plot. A deterministic sensitivity analysis will be performed for the cost and efficiency data that appear not robust.

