## Study design

This is a pragmatic stepped-wedge randomised controlled study of the Acti-Pair programme implementation in eight French departments, that is, eight clusters, each composed of one DAPAP, operating in the area defined by the department it is located. The intervention will be deployed in a random order, successively in the various clusters, across three stages (control, transition and interventional stages). First, all clusters start in the control and sequentially transition into the intervention (the Acti-Pair programme) until all clusters have received the intervention. Participants will be recruited successively in patients' control and intervention stages and the transition stage for peers.

The stepped-wedge design is presented in figure 3.

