### Health economic evaluation

A cost-utility analysis and a cost-effectiveness analysis will be performed in this study, as recommended by the French National Authority of Health (HAS, https://www.has-sante.fr/). These analyses will estimate (1) the cost per quality-adjusted life year (QALY) gained and (2) the cost per patient continuing PA at 12 months, thanks to the implementation of the intervention. The efficacy data will be those collected by the study: quality of life (using the EQ-5D-5L questionnaire) and mortality data, if any, transformed into utilities to calculate QALYs and the number of patients continuing PA at 12 months. Cost data will be collected throughout the study in the eight departments involved. The analysis will be conducted from the payer’s (health insurance) perspective. The time horizon will be the study duration (12 months), and per French guidelines (HAS, https://www.has-sante.fr/), no discount rate will be applied. The health economic analysis will include all patients participating in the study. The costs will include direct medical costs (general practitioner consultations, APA sessions, peer patients and APA professionals) and indirect costs related to the implementation of the intervention (training, rental of premises and equipment and running costs).

The outcomes and timeline are presented in table 2.

**Table 2 T2:** Outcomes and timelines for patients, peers and professionals

	Inclusion	Control or intervention phase	3-month visit	6-month visit	12-month visit
Patients					
Consent form signature	x				
TM6	x		x	x	x
Muscular strength	x		x	x	x
FACIT-F questionnaire	x		x	x	x
APAQ questionnaire	x		x	x	x
EQ-5D questionnaire	x		x	x	x
BREQ-2 questionnaire	x		x	x	x
Actigraph GT9x, Pensacola, Florida, USA	x		x	x	x
Heart rate monitor	x		x	x	x
Medicoeconomic evaluation			x	x	x
Only for patients in the intervention phase					
WAI scale					x
Satisfaction questionnaire					x
Population reach					x
Programme adhesion					x

Peers	Inclusion	Training	End of the intervention phase
Consent form signature	X		X
6 MWT	X		X
Muscular strength	X		X
FACIT-F questionnaire	X		X
APAQ questionnaire	X		X
EQ-5D questionnaire	X		X
BREQ-2 questionnaire	X		X
Actigraph GT9x, Pensacola, Florida, USA	X		X
Heart rate monitor	X		X
Training and programme satisfaction		X	X
Adaptation: semidirective interviews	X		X
Population reach			x

Professionals	Control phase	Transition phase	Intervention phase

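### The ICERs are defined as differences in group means with no calendar-period or department term, although programme patients enter later by design, and the bootstrap is not said to respect departments

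*Protocol article*

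**What the plan says.** The Health economic analysis section of the protocol article gives one rule for the cost-utility and the cost-effectiveness ratio. Each is "calculated by dividing the difference in mean costs between the intervention group and the control group by the difference in mean effectiveness". On uncertainty it says: "Using the non-parametric bootstrap method, statistical uncertainty will be considered to construct a 95% CI and a scatter plot". The only sensitivity analysis is this: "A deterministic sensitivity analysis will be performed for the cost and efficiency data that appear not robust". It adds: "These ICERs will also be produced for each department to complete the context analysis". The effectiveness unit, in Health economic evaluation, is "the number of patients continuing PA at 12 months".

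Under Study design there are "eight clusters, each composed of one DAPAP", and "all clusters start in the control and sequentially transition into the intervention (the Acti-Pair programme) until all clusters have received the intervention". On enrolment: "Participants will be recruited successively in patients' control and intervention stages and the transition stage for peers".

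The quantitative Data analysis section treats the activity outcome differently. It plans a random intercept for department and examines a calendar-time variable (five six-month periods), which may stay in the model if a trend is found. Secondary endpoints get a similar model. Costs, QALYs and ICERs are not named there.

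**The concern.** In a one-way stepped wedge, time and treatment are linked: control patients are concentrated early and programme patients late. A difference in group means therefore mixes the programme's effect with whatever else changed in between, such as resource use, utilities or background activity. The article allows for this in the activity outcome, but the ICER rule contains no such term, and a deterministic sensitivity analysis addresses neither time nor clustering. The same section also refers to a placebo arm, which this trial does not have, so its wording may not have been fitted to the design.

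Within one department, control always comes first, so a department ICER has no concurrent comparator at all.

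The bootstrap raises a second question. If patients are resampled as though independent, variation between departments is left out of the interval.

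Efficiency is a stated secondary objective and is meant to inform decision-makers about transfer of the programme. At stake is whether cost per QALY and cost per active patient are attributable to the programme, and whether their stated precision is honest.

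**Working it through.** **Inputs from the article.** 8 departments; 3 sequences of 2 or 3 departments; 5 periods of 6 months; 692 patients before drop-out; ICC 0.04 (Sample size, for MVPA). No ICER or interval is stated, so there is no plan figure to reproduce.

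**Assumptions.** Figure 3 is not shown. I take C T I I I / C C T I I / C C C T I (C control, T transition, I intervention), with no patients enrolled in T and equal department-periods. That gives 32 enrolling cells of 692/32 = 21.6 patients. The ICC for costs or QALYs is not given, so a range is shown.

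**1. Calendar gap.** With 3, 3 and 2 departments per sequence:
- Control: 15 cells, mean period (3×1 + 3×3 + 2×6)/15 = 24/15 = 1.60.
- Programme: 17 cells, mean period (3×12 + 3×9 + 2×5)/17 = 73/17 = 4.29.
- Gap 2.69 periods, × 6 = 16.2 months.

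With 3, 2 and 3 departments: 69/16 − 27/16 = 2.625 periods, or 15.8 months. Other layouts tried gave 1.6 to 3.0 periods, about 10 to 18 months.

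**2. Bias from drift.** A linear drift of d per period shifts each crude difference by about 2.6d to 2.7d. In a simulation (no true effect, SD 1, 704 patients, ICC 0.04, patient-level bootstrap), an assumed drift of 0.05 SD per period gave a bias of 0.14 SD and 52.5% coverage. A drift of 0.10 SD gave 0.26 SD and 11.7%. These drifts are illustrations; the article documents no trend.

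**3. Within a department.** Mean programme period minus mean control period is 4 − 1, 4.5 − 1.5 and 5 − 2 in the three sequences. Each is 3 periods, or 18 months, with no overlap.

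**4. Clustering, if patients are resampled as independent.** For total variance 1, ICC ρ, and department j's share of each arm w:
- True variance = ρ Σ(w_Ij − w_Cj)² + (1 − ρ)(1/n_I + 1/n_C).
- Patient-level bootstrap target = 1/n_I + 1/n_C.

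For 3, 2 and 3 departments, n_I = n_C = 346. The share differences are 2/16, 0 and −2/16, so the sum of squares is 6 × 0.015625 = 0.09375.
- True: 0.04 × 0.09375 + 0.96 × 0.005780 = 0.00930.
- Target: 0.00578.
- SE ratio √(0.00930/0.00578) = 1.27; coverage 2Φ(1.96/1.268) − 1 = 87.8%.

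| ICC | SE ratio, true/bootstrap | Coverage, formula | Coverage, simulation |
|---|---|---|---|
| 0.01 | 1.06–1.07 | 93–94% | 92.7% |
| 0.04 | 1.22–1.27 | 88–89% | 86.2% |
| 0.10 | 1.49–1.59 | 78–81% | 74.9% |

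The ranges cover the possible splits of departments over sequences. The simulation benchmark at ICC 0 was 93.6%.

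**5. When the clustering problem disappears.** If every department contributes equally to both arms, the share differences are zero and the ratio is √(1 − ρ) = √0.96 = 0.98. Simulated coverage was 93.3%, the same as the benchmark. With a cluster autocorrelation of 0.8 the ratio is 1.06.

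Cancellation requires the department effect to be common to both arms. Training, premises and running costs are recorded by department and arise mainly under the programme. A department component in the programme arm only, with equal shares of 1/8 (sum of squares 0.125), gives [0.04 × 0.125 + (0.96 + 1) × 0.002890]/0.005780 = 1.845, so an SE ratio of 1.36 at a variance share of 0.04. At a share of 0.10 it is 1.76.

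**The case against.** The strongest defence is that a ratio of mean differences is simply what an ICER is, and that the means could be model-adjusted. A condensed article may also leave the resampling unit to the full plan. The second part stands. A reader might infer that the plan commits to a patient-level bootstrap and that its intervals are therefore too narrow. The text does not say so, and the narrowing also depends on an unbalanced layout and on an ICC given only for MVPA. The first part is weaker: the section sets its own rule, names the groups whose means are compared, and mentions no adjustment. No later plan can give a single department a concurrent control.

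The mixed model for secondary endpoints arguably covers EQ-5D, which is a listed impact outcome. That stands for EQ-5D scores but does not reach costs, QALYs or the ICERs.

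Consultation fees are valued at the conventional rate and sessions at a unit cost based on average salary, which limits price drift. That is fair, but drift in resource use, utilities and activity remains. A reader might infer that the ICERs will be biased in a known direction. With no trend documented, neither sign nor size can be stated.

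Department ICERs are offered only for context. A reader might expect them to be used as performance rankings, but nothing in the article says so.

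The unit of patients continuing activity is not contradictory: entry requires under 150 minutes a week, not none, and the programme aims to start as well as maintain activity. The cut-off is nevertheless not attached to it.

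**Conclusion.** The point holds for calendar time. As written, the ICER rule has no protection against secular change in a design that places programme patients about 16 months after controls (assumed layout; 10 to 18 months across those tried). The department ICERs are before-after comparisons, which follows from the one-way crossover and needs no layout assumption.

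For clustering, the point is conditional. Only if patients are resampled as independent, under the assumed layout and with the MVPA ICC of 0.04 carried over to costs or QALYs, is the true SE 1.22 to 1.27 times the bootstrap SE, with coverage of about 86 to 89%. With equal department contributions to both arms there is little or no undercoverage from shared department effects. It should be corrected before the economic analysis is run; the primary clinical analysis is not affected.

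**What to change.** - Estimate incremental cost and incremental effect from mixed models with treatment, calendar period of enrolment and a random department effect. Include period always, not only when a trend is detected. Adjust QALYs for the baseline EQ-5D utility, which is already collected.
- Take uncertainty from those models, for example net-benefit regression over a range of willingness-to-pay values with a small-sample correction for 8 clusters. A patient-level bootstrap should not be used. Resampling departments within sequences is no remedy either: with 2 or 3 departments it recovers only (k − 1)/k, one half to two thirds, of the between-department variance.
- Report department-level costs and effects descriptively, without ICERs.
- Define the effectiveness unit as MVPA of at least 7.5 MET-hours/week by actimetry at 12 months, the threshold already given under Primary outcome.

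No new data are needed. The cost is plan wording, modest extra programming and wider intervals.

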### Data analysis

#### Quantitative outcomes analysis

The statistical analysis will be performed on the intention-to-treat population. The statistical significance will be a two-sided alpha level of 5%. Statistical analyses will be performed using SAS software (SAS-Windows version 9.4 on computer PC) and R software version 4.2.1 on computer. The characteristics of the population will be described using quantitative variables, including the mean and SD, and qualitative variables, such as the number of cases and percentages. The Acti-Pair programme’s effect on the PA level will be analysed using a mixed-effects model with a random intercept per department to consider the correlation of the level of PA between patients of the same department and a random effect on the initial value of PA. This random effect will depend on both the cluster and the patient (random effect of the patient nested in the cluster). The model will consider the fixed effect of the treatment group (Acti-Pair programme or usual care). The possible evolution of the evaluation criterion over time will be analysed by introducing a calendar time variable into the mixed-effects regression model (5 periods of 6 months, see figure 3). If a trend is identified, the calendar time variable can be introduced into the model as an ordinal variable. This analysis will make it possible to quantify the effect of the Acti-Pair programme after adjustment for a possible time effect. An interaction between the effect of the treatment group and the random ordinal by the department may be added to quantify any heterogeneity in the benefit of the Acti-Pair programme. An initial model will be built without additional adjustment. If an imbalance between the groups is observed, a second model will be built by adjusting the variable(s) on which the imbalance is observed (sensitivity analysis). A possible logarithmic transformation of the evaluation criterion could also be considered to satisfy the normality assumption of the linear mixed-effects model.

For the analysis of the secondary endpoints, no p value will be given, and only the 95% CIs of the efficacy indices will be estimated.^28^ It will be carried out using a mixed-effects model similar to the one used for the primary endpoint. No interim analysis is planned.

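### The incremental QALY is defined only as a difference in group means, with no stated adjustment for the EQ-5D-5L utility collected at inclusion

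*Protocol article*

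**What the plan says.** The Health economic analysis section obtains both ratios by "dividing the difference in mean costs between the intervention group and the control group by the difference in mean effectiveness". On the effect side of the cost-utility ratio it says: "QALYs will be calculated based on responses to the EQ-5D-5L questionnaire, transformed into utilities and mortality data obtained during the study, if any". On uncertainty it says: "Using the non-parametric bootstrap method, statistical uncertainty will be considered to construct a 95% CI and a scatter plot". It names no regression and no covariate. The ratios are also to be produced for each department.

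Table 2, in the Health economic evaluation section, marks the EQ-5D for patients at all four visits: inclusion, 3, 6 and 12 months. A utility at entry will therefore exist for each patient who completes the questionnaire.

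The Quantitative outcomes analysis section does deal with initial values, calendar time and imbalance, but for the clinical outcomes. Its initial-value term is "a random effect on the initial value of PA", that is, of physical activity. If the groups are seen to differ, a second model adjusted for the unbalanced variables is fitted as a sensitivity analysis. For secondary endpoints the section says: "It will be carried out using a mixed-effects model similar to the one used for the primary endpoint". Nothing there or in the health-economic sections extends that model to QALYs.

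**The concern.** A 12-month QALY built from these visits contains the patient's utility at entry, and his later utilities are correlated with it. If the groups differ at entry, a plain difference in mean QALYs carries part of that difference into the result: directly through the first interval, and indirectly through the later visits.

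Equal entry utility cannot be taken for granted here. The Study design section has eight departments moving from control to intervention, with patients recruited successively in each stage. The Randomisation section says that the study is not blinded. Recruitment runs through physicians, associations, the DAPAPs and flyers, so the department's stage may be known when a patient is approached. Patients attracted by peer support may differ at entry from those offered advice alone.

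Cost per QALY gained is one of the two health-economic endpoints, and the incremental QALY is its denominator. The per-department ratios rest on fewer patients each and are more exposed.

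**Working it through.** The plan gives no figure for the QALY comparison, so there is none to reproduce. The check asks how much of an entry difference an unadjusted comparison would pass on.

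**Inputs from the article**
- EQ-5D at 0, 3, 6 and 12 months (Table 2).
- Horizon: "The time horizon corresponding to the study period is 12 months; no discounting will be performed, as recommended".
- 346 patients per group and 692 in total before drop-out, intracluster correlation 0.04, average cluster size 58 (Sample size).
- Eight departments (Study design).

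**Assumptions, not in the article**
- QALY as the trapezoid area under the four utilities.
- Equal utility variance at each visit, and a common between-visit correlation ρ of 0.3 to 0.7.
- Utility SD of 0.15 to 0.25.
- For scale only: an entry difference of 0.02, and a programme gain of 0.03 at every follow-up visit.

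**Weights.** The intervals are 0.25, 0.25 and 0.5 years:
- 0 months: 0.25/2 = 0.125
- 3 months: (0.25 + 0.25)/2 = 0.25
- 6 months: (0.25 + 0.5)/2 = 0.375
- 12 months: 0.5/2 = 0.25

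**Share passed on.** An entry difference d adds 0.125·d directly and 0.875·ρ·d through the later visits, so the share is 0.125 + 0.875ρ. This describes a chance difference among like patients. A lasting difference between the populations recruited in the two stages could persist more strongly, and covariate adjustment would then remove only part of it.

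**Scale.** A gain of 0.03 at each follow-up visit is worth 0.03 × 0.875 = 0.026 QALY.

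**Precision.** For unit-variance utilities, Var(QALY) = 0.28125 + 0.71875ρ and R² = (0.125 + 0.875ρ)² / Var(QALY). The adjusted standard error is √(1 − R²) times the unadjusted one. This is at individual level, with no clustering.

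| ρ | Share passed on | Shift for d = 0.02 | Shift / 0.026 | R² | SE ratio |
|---|---|---|---|---|---|
| 0.3 | 0.39 | 0.008 | 30% | 0.30 | 0.84 |
| 0.5 | 0.56 | 0.011 | 43% | 0.49 | 0.71 |
| 0.7 | 0.74 | 0.015 | 56% | 0.69 | 0.55 |

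**Is an entry difference of 0.02 plausible?** The standard error of a chance difference is SD × √(2/346). That gives 0.011 at SD 0.15, 0.015 at SD 0.20 and 0.019 at SD 0.25, if patients are independent. As a rough guide to clustering, the parallel-cluster design effect is 1 + 57 × 0.04 = 3.28, which multiplies these by √3.28 = 1.81 and gives 0.021 to 0.034. The 0.04 was set for physical activity and the formula is not a stepped-wedge one, so this is indicative only. On either basis, 0.02 is within ordinary chance.

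**Single department.** 692/8 = 86.5 patients, or about 43 per stage if evenly split. With SD 0.2, the chance standard error of the entry difference is 0.2 × √(2/43) = 0.043. Multiplied by the shares above, this is 0.017, 0.024 and 0.032 QALY, from about two thirds of the 0.026 used for scale to more than all of it.

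**The case against.** The strongest reply is that the article is silent on adjustment and that silence is not a choice. The quoted rule is the usual definition of an incremental ratio. A regression-adjusted difference in mean QALYs would satisfy it, and a condensed article may leave such detail to a fuller health-economic plan. This stands in part: a reader might infer that the trial will use a raw difference, but the text never says raw or unadjusted. What remains is that the section sets out the ratio, the source of the QALYs and the bootstrap, and names no covariate, while the same article specifies its clinical model in some detail.

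A reader might also say that inclusion utility is ignored, or that the whole of any entry difference is counted as QALYs gained or lost. Neither is supported. With an area-under-the-curve QALY, inclusion utility enters with weight 0.125, and under the assumptions used only part of a chance difference passes through.

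A large loss of precision or power is likewise not established. The SE ratios rest on assumed individual-level correlations. With eight departments, variation between departments may make the gain smaller. No QALY test or power target is planned.

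Finally, the clinical analysis does recognise initial values and imbalance. But its initial-value term concerns physical activity, and its imbalance rule yields only a sensitivity model. Even if carried over to QALYs, it would leave the main comparison without a stated adjustment for entry utility.

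**Conclusion.** The point holds as a gap in the stated estimator that is cheap to close, not as a proven error. Followed as written, the Health economic analysis section would let about 39% to 74% of an entry difference in utility pass into the incremental QALY, given a trapezoid QALY and a between-visit correlation of 0.3 to 0.7. The documents give neither. The percentages of programme effect depend further on an assumed 0.02 entry difference and an assumed 0.03 gain, and serve only for scale. Adjustment would also be expected to narrow the interval, but the documents do not allow the amount to be fixed. No figure printed in the article changes.

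**What to change.** In the Health economic analysis section, state that the incremental QALY is the treatment coefficient from a regression of each patient's 12-month QALY on group and inclusion EQ-5D-5L utility, with department and calendar-period terms in line with the Quantitative outcomes analysis section. Those terms are needed because group is tied to calendar time in a stepped wedge; group and inclusion utility alone would not reflect the design. Use this estimate in the cost-utility ratio, refit it in every bootstrap replicate, and show the unadjusted difference as a sensitivity result.

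For the per-department ratios, adjust for inclusion utility within the department and present them as descriptive, since each compares an earlier with a later stage in few patients.

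The change costs a few sentences and some regression terms. It needs no new data or patients. The small downside is that patients with a missing inclusion EQ-5D need a simple imputation to stay in the model. If a fuller health-economic plan already contains this adjustment, it is enough to say so here.
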